#### Cost data collection

We will collect micro-costs^44^ on the following components of the pathway:

Item costs for ELF and FIB-4 tests and venepuncture costs.Nursing time for: venepuncture, VCTE, results delivery and onward referral.Cost per VCTE assessment including equipment, equipment servicing and training.Community venue hire for liver assessment.

### Data management plan

Participant data will be managed according to the study data management plan which is available on the study website (reflexstudy.org). Study data, including participant-identifiable data will be stored securely by ethical approvals.

### Data analysis

#### Primary outcome

We will conduct an ‘intention to diagnose’ analysis for the primary outcome where all participants undergoing randomisation will be analysed within the group to which they were assigned, regardless of whether they engaged with the diagnostic process following referral within their study arm. Logistic regression will be used to compare the binary outcome between the standard care and intervention arms. Exact or penalised likelihood estimation methods will be used to avoid the small-sample bias that otherwise would be present with such small, expected outcome numbers. Loss to follow-up (LTFU) and missing data will be managed by our LTFU management plan (see online supplemental material).

#### Cost-effectiveness analysis

For the cost-effectiveness evaluation, data from the study will be incorporated into a decision analytical model (developed in Microsoft Excel). These data include: the micro-costs of testing and follow-up, drop-out rates from the diagnostic pathways (usual care and screening), the relative proportions of different stages of liver disease and the demographic characteristics of the cohorts.

The model will consist of a decision tree for the diagnostic process and a Markov state transition model for the long-term disease process (figure 2). It will estimate the quality-adjusted life years (QALYs) and costs associated with liver disease. The model structure will be similar to previous models for HCC surveillance (eg,^34 36^) and calculate the difference in costs and QALYs between different testing approaches and no testing. Patients with characteristics based on our study population and study outcomes will enter the model. The model will have 1 year cycles and a lifetime horizon (ie until the cohort age is 100 years). Costs will be calculated using an NHS and Personal Social Services perspective. Costs and utilities for the model health states will be taken from a targeted review of the medical literature.

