**Methods and analysis:**

The study will use a multi-centre, unblinded individual randomised controlled trial design. The aim will be to determine the effectiveness and cost-effectiveness of screening all adults with T2DM to identify those at high risk of HCC. The recruitment strategy has been supported by patient and public involvement (PPI). Participants will be identified via an automated search of primary care records and invited to participate via text. 320 participants will be randomised for screening. The screening will include measurement of bio-markers for liver fibrosis (ELF and Fib-4) and vibration-controlled transient elastography. Another 320 participants will be randomised to standard care. Demographic and medical history data will be collected at baseline from all participants. Outcome data will be collected remotely from healthcare records. The primary outcome is the proportion of participants in each arm who are referred to HCC surveillance following testing for liver disease within 12 months of randomisation. The results will be used to calculate the incremental cost-effectiveness ratio of screening via a Markov model.

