However, there are challenges with extrapolating prior models to a real-world intervention such as the NHSE pilot that aims to test a broader range of adults with T2DM for liver disease as part of routine care. First, we do not know the characteristics of patients who will respond to an invitation from primary care for liver assessment. These characteristics are important—it is likely that patient age and comorbidities will influence their probability of having liver disease and their personal gain from an early diagnosis. Second, we do not know what proportion of this cohort meets clinical criteria for interventions that convey the advantage of early diagnosis, for example, what proportion enter an HCC surveillance pathway and what proportion have clinically significant portal hypertension and are started on beta blockers. Third, we do not know the real-world performance of standard care in the UK. Most patients with T2DM do not get tested for liver disease, despite their heightened risk because they are not assessed for the additional risk factors that are needed to qualify for testing. For example, LFTs are not part of an annual diabetes check-up in the UK and may or may not be measured when patients are considered for statin treatment; liver ultrasound is not a routine test, and alcohol consumption is not accurately or consistently assessed in primary care. Finally, previous economic evaluations are outdated as they use primary-care-based assessments (eg history and examination) that do not incorporate tests for fibrosis (eg Fib-4 and VCTE). Since the NICE NAFLD Guideline in 2016, tests for liver fibrosis have widely integrated into community diagnostic pathways for liver disease and therefore in future studies, models of ‘usual care’ need to reflect this.

This study protocol describes a randomised controlled trial with a nested cost-effectiveness evaluation. The study aims to compare the number of participants referred for HCC surveillance between an intervention where patients with T2DM are universally offered screening for liver disease against usual care.

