## Method and analysis

The trial is described in accordance with the SPIRIT checklist.^37^ The design will be an unblinded randomised controlled trial with a nested cost-effectiveness evaluation comparing the offer of screening to *all* patients with T2DM for liver disease against standard care. We will proceed straight to an effectiveness evaluation rather than conducting a formal feasibility/pilot study. We justify this approach because the components of the intervention (used in testing for liver disease in patients with standard risk factors (eg abnormal blood results or harmful alcohol consumption)) are widely implemented. Additionally, data such as the attrition rate from the conventional diagnostic pathway is already known (see sample size section).^38^ Undertaking a randomised controlled trial in this setting is very important as this provides a contemporaneous standard care arm as a counterfactual.

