### Participant identification

Primary care centres will identify potential participants from their patient records. The research team will provide these practices with a search query to run on their patient management systems (SystmOne or EMIS) (see online supplemental material and trial website (reflexstudy.org)). Flagged patients will be screened for eligibility by practice staff. The patients on the list of potential participants will be sent a text advising them about the study, where they can access further information and who to contact if they would like to self-refer their interest in participating (see online supplemental materials).

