### Consent and randomisation

If a participant contacts the research team, they will be sent an information sheet and given time to consider participation before providing written consent to the research team (see online supplemental material). After giving consent, each participant will be randomised. To ensure equal numbers of patients within each arm of the study, we will use block randomisation with a block size of 4. Blocks will be used to ensure a balance between the participants in each arm of the study—strata will be sex, age group and alcohol consumption. This will be managed by the Southampton NIHR Biomedical Research Centre team using randomisation software.^39^

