## Discussion

The application, effectiveness and cost-effectiveness of screening for liver disease in patients with T2DM have not been well studied. Despite this, it is now recommended practice in some countries and subject to national clinical pilots in others. We aim to fill this knowledge gap.

The robust assessment via randomised controlled trial of a screening intervention for liver disease in T2DM with an objective primary outcome that is assessed independently of the researchers will have a significant impact. If effective, the trial would provide evidence to justify widespread screening in an enormous and growing proportion of the global population with a reduction in liver death. If not effective, it could prevent further rollout of a massive, costly programme of work that will have significant resource implications for health service systems. Looking forward, the trial will also quantify the effect size required and suitable pricing for novel anti-fibrotic therapies to meet cost-effectiveness thresholds.

A strength of the study design is the incorporation of a usual care arm that is a diverse representation of standard practice where testing for liver disease is applied to a few, selected patients with T2DM. The design therefore allows for real-world comparisons between the status quo and (via the intervention arm) a close representation of what a screening programme for liver disease in patients with T2DM might look like.

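### The question is an offer of screening to all adults with type 2 diabetes, but the model's drop-out rates and the listed micro-costs start after consent, so invitation cost and non-uptake are left out

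*Protocol article*

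**What the plan says.** **The question.** The Abstract aims to "determine the effectiveness and cost-effectiveness of screening all adults with T2DM". The end of the Introduction describes "an intervention where patients with T2DM are universally offered screening for liver disease against usual care", and Method and analysis speaks of "comparing the offer of screening to *all* patients with T2DM for liver disease against standard care". One modelled strategy in Cost-effectiveness analysis offers elastography (VCTE) to everyone.

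**Who is randomised.** Under Participant identification, practices run a record search, staff check eligibility, and patients receive a text that says "who to contact if they would like to self-refer their interest in participating". Consent and randomisation then adds an information sheet and written consent: "After giving consent, each participant will be randomised".

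**What enters the model.** Cost-effectiveness analysis lists testing and follow-up costs, "drop-out rates from the diagnostic pathways (usual care and screening", disease-stage proportions and demographics. The modelled patients are based on the study population.

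**What is costed.** Cost data collection names test items, venepuncture, "Nursing time for: venepuncture, VCTE, results delivery and onward referral", VCTE equipment and training, and venue hire.

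**What is claimed.** Strengths and limitations promises definitive cost-effectiveness in a real-world setting. The Discussion calls the intervention arm "a close representation of what a screening programme for liver disease in patients with T2DM might look like". Secondary outcomes include cancer deaths avoided by screening, with no denominator stated.

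**The concern.** People who ignore or decline the offer are lost before randomisation. The intention-to-diagnose analysis keeps everyone from randomisation onward, and pathway drop-out is counted among people who have already volunteered. Neither can measure non-uptake.

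The cost list has the same starting point. The Introduction describes the NHS England pilot as a primary care search followed by invitation, and the trial's own recruitment uses a search, an eligibility check and a text. The modelled strategies are meant to reflect current local testing and that pilot, from an NHS and Personal Social Services perspective. Invitation is therefore a programme step with a cost, and that cost is incurred for every person invited, whether or not they attend.

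At stake are the ICER and cost per case for the screening strategies, and how a reader interprets the number of deaths avoided.

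**Working it through.** **Inputs from the article.** Sample size gives planning drop-out *d* of 5% (called realistic) and 25% (conservative). The stated power cannot be reproduced from the text, because the arm event rates are not given there; this point does not depend on it. The article gives no uptake and no invitation cost.

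**Assumed inputs.** Uptake *u*, the share of invited people who respond and consent: 5% to 50%. Invitation cost *c* per person invited (search, eligibility check, text): £1 or £5. Incremental cost *C* per consenter: £150. Incremental QALYs *Q* per consenter: 0.015. These give an illustrative ICER of 150/0.015 = £10,000 per QALY before invitation is costed.

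**Step 1: coverage of those invited.** Coverage = *u* × (1 − *d*). At 10% uptake this is 0.10 × 0.95 = 9.5% with 5% drop-out and 0.10 × 0.75 = 7.5% with 25%. Pathway drop-out moves coverage far less than uptake does, so it cannot stand in for it.

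**Step 2: ICER per person invited.**

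(*u* × *C* + *c*) / (*u* × *Q*) = *C*/*Q* + *c*/(*u* × *Q*)

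With *c* = 0, *u* cancels. With *c* > 0, the ICER rises by the proportion *c*/(*u* × *C*). Example: (0.10 × 150 + 5)/(0.10 × 0.015) = 20/0.0015 = £13,333, a rise of 33.3%.

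**Step 3: cost per case.** If *y* is the number of cases found per consenter, the omitted amount is *c*/(*u* × *y*), that is, *c*/*u* per consenter divided by yield.

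**Step 4: deaths avoided.** If consenters avoid *b* deaths each and selection is neutral, a programme inviting *N* people avoids *N* × *u* × *b*. Applying the consenter result to all *N* gives *N* × *b*, which is 1/*u* times too many.

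| Uptake | Coverage, 5% drop-out | Coverage, 25% drop-out | Omitted cost per consenter, *c* = £1 / £5 | ICER rise, *c* = £1 / £5 | Overstatement of deaths avoided, only if applied to all eligible |
|---|---|---|---|---|---|
| 5% | 4.75% | 3.75% | £20 / £100 | 13.3% / 66.7% | 20-fold |
| 10% | 9.5% | 7.5% | £10 / £50 | 6.7% / 33.3% | 10-fold |
| 20% | 19% | 15% | £5 / £25 | 3.3% / 16.7% | 5-fold |
| 50% | 47.5% | 37.5% | £2 / £10 | 1.3% / 6.7% | 2-fold |

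**Step 5: selection of responders.** If yield among programme attenders is *r* times that among trial consenters, the ICER scales roughly by 1/*r*: *r* = 0.5 doubles it and *r* = 1.5 multiplies it by 0.67. The article does not allow the direction to be determined.

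**The case against.** The strongest reply is that the plan makes no population projection. The model is populated from the study cohort, and deaths avoided are simply a model output. Responders are also the group of interest: the Introduction names the characteristics of people who answer a primary care invitation as the first unknown. Offering VCTE to everyone distinguishes that strategy from the FIB-4-first and ELF-first ones; it does not assert full uptake. Randomising after consent is normal in an individually consented trial. The list of model data is introduced as inclusive, not exhaustive. The model figures are not shown, a fuller economic plan may hold an uptake step, and scenario analyses of the main assumptions are already promised.

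Most of this stands. A reader might infer that the plan overstates population benefit several-fold. The article does not support that, because it states no scaling of consenter results to all eligible adults. Nor can a fold figure be built on the 5% drop-out: that is a power-planning remark, and the model is to use drop-out observed in the study. A reader might also suppose that low uptake in itself worsens cost per QALY. It does not, since non-responders add neither testing cost nor benefit.

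The reply does not remove the cost gap. Unlike the list of model data, the micro-cost list is worded as the components to be collected, and it starts at testing although the article itself makes search and invitation part of the pathway. Nor does it remove the distance between a universal offer and a randomised group of consenting responders, which the stated limitations do not mention.

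**Conclusion.** The point holds in limited form. The comparison between arms remains valid for consenting responders. Trial drop-out cannot represent non-uptake of the offer, and the cost list as written would leave invitation cost divided by uptake out of the ICER and cost per case for screening.

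Under the assumed values the ICER effect runs from about 1% (£1 per invitation, 50% uptake) to 67% (£5, 5% uptake). It is small unless uptake is low or invitation is costly. These sizes rest entirely on assumed uptake, invitation cost and incremental cost per consenter.

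Overstatement of deaths avoided by about 1/uptake is conditional on applying consenter results to all eligible adults. The wording about a definitive answer and about closeness to a real programme invites that use, but the plan does not commit to it. Responder selection could shift results either way, so no net direction of bias is claimed.

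**What to change.** - Add record-search, eligibility-check and invitation cost per person invited to Cost data collection and to the screening branch of the decision tree.
- Ask practices to return aggregate counts from the search they already run: flagged, eligible, texted, responded, consented.
- Include uptake as a model parameter varied over a wide range in the sensitivity analysis. Use the trial's response rate as one scenario and not as the base case, because answering a research text with self-referral and written consent is not the same as accepting a programme invitation.
- Report deaths avoided both per person invited and per person screened.
- Limit the claims in Strengths and limitations and in the Discussion to consenting responders.

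The cost is a small amount of extra data collection from 16–20 practices and two more model inputs. The cost per case and ICER will look slightly less favourable, or more than slightly if uptake proves low.

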**Figure 2 F2:**
[figure not shown]
Markov model structure is used to calculate the incremental cost-effectiveness of different testing strategies. The findings from the trial will parameterise this model. Numbers 1–4 correspond to the benefits of early detection that will be incorporated into the modelling. HCC, hepatocellular carcinoma.

Our base-case analysis will closely match real-world practice. In both cohorts, patients identified with liver cirrhosis and referred for HCC surveillance will enter a separate health state—named F4_SURV. Based on recently published data, participants in this health state who develop HCC will have a higher chance of cure (ie return to their original F4 SURV health state) and a lower chance of progression to death or transplantation.^16^ Similarly, a proportion of those in F4_SURV will have a lower risk of progressing to a decompensated state that reflects the real-world number of participants who commence B blockers by recent guidelines.^45 46^ Participants identified with F2 or F3 disease will enter monitoring states (F2_Mon and F3_Mon) and undergo biannual assessment for progression to F4 disease. Monitoring will stop when participants in the model reach 80 years of age.

As part of our base case analysis, we will calculate the cost-effectiveness (cost per QALY) of four testing strategies that are broadly reflective of current testing strategies in the study region and the NHSE pilot (described in the background). These will be compared against ‘no testing’ and presented as ICERs that can then be compared between strategies.

Usual care.Reflex testing with VCTE only (ie everyone offered VCTE).FIB-4 then VCTE for patients with FIB-4>3.25.ELF then VCTE for patients with an ELF >9.5.

We will conduct probabilistic sensitivity analyses where model parameters are probabilistically varied across pre-specified distributions and ranges. The results of the probabilistic sensitivity analyses will be presented as a scatter plot and a cost-effectiveness acceptability curve.

Finally, we will conduct a one-way sensitivity analysis varying the input parameters in the model and scenarios around the main model assumptions. Specifically, we will test a scenario where we introduce a hypothetical anti-fibrotic agent that is given to patients in the F2_Mon and F3_Mon health states. As part of this, we will conduct a threshold analysis where we will calculate ICERs for the hypothetical drug at different levels of therapeutic effectiveness. Anti-fibrotic therapy is not part of our base-case analysis as it is not currently part of usual care in England. Figure 3 shows a study flow chart showing how the study arms and nested cost-effectiveness evaluation are linked. The rationale for the study sample size is also conveyed.

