## Introduction

 Cancer is the leading cause of mortality in patients with type 2 diabetes mellitus (T2DM)^1^ and is strongly associated with site-specific cancers including hepatocellular carcinoma (HCC).^2^ 830 200 people died from HCC in 2020, and the incidence of HCC is expected to increase by 55% in the next 20 years.^3^ HCC is now the fastest growing indication for liver transplantation,^4^ and it is expected to become the third most common cause of cancer death worldwide by 2030.^5^ HCC has a very poor prognosis with a 5-year survival of ~20%.^6^ However, if cases are identified at an early stage, curative treatments are available which include surgical resection, liver transplant or tumour ablation.^6^

A major driver for the increasing number of deaths from HCC is the increasing global prevalence of T2DM.^3 5 7^ T2DM causes liver steatosis, inflammation, fibrosis and liver cirrhosis and patients with significant liver fibrosis or cirrhosis are at risk of HCC.^8 9^ There is a high prevalence of all stages of liver disease in people living with T2DM.^10^,^14^

International guidance recommends biannual surveillance for HCC in patients with liver cirrhosis via ultrasound imaging; however, less than one-third of incident cases of HCC in patients with T2DM are identified via surveillance.^15^ Identification of HCC via surveillance is important as cancers that are identified in patients who are undergoing regular surveillance have better outcomes.^16^ To engage patients with T2DM with HCC surveillance, it is necessary to first identify patients with cirrhosis. In the past, liver disease was hard to identify because it progresses without signs or symptoms. However, several approaches have now been validated in patients with T2DM to identify asymptomatic disease. These include the utilisation of blood tests such as the Fibrosis-4 test (FIB-4)^17^ and the Enhanced Liver Fibrosis (ELF) test,^18^ as well as a simple scan of the liver which uses vibration-controlled transient elastography (VCTE) to assess the liver stiffness^1719^,^21^ as a validated marker of fibrosis.

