### Primary outcome

The number of participants referred to secondary care with the suspected liver disease within 12 months of randomisation who are subsequently referred for HCC surveillance.

As an unblinded trial, it is important our primary outcome is as objective as possible and independent of the research team. In both study arms, patients with high liver stiffness measurements will be referred to nearby hepatology services (with thresholds defined by local practice). Via usual care, an independent local clinician will then assess the severity of liver disease. In real-world practice, this may include history, examination, no further tests or repeat VCTE, additional tests for fibrosis and in some cases liver biopsy. Regardless of the clinical approach taken, the primary outcome will be whether the clinician felt the disease was severe enough to warrant referral for HCC surveillance. Since the trial sites cover a variety of different regions across the south of England, this pragmatic approach is likely to closely reflect current UK practice.

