#### Primary outcome data collection

The primary outcome—referral to HCC surveillance following a referral with suspected liver disease from primary care will be assessed by the research team from each participant’s healthcare records. Participants will not need to be recontacted for outcome data. For standard care participants, the primary care record will be reviewed for a referral letter to secondary care or a community liver assessment service that was sent within 12 months of randomisation. For both trial arms, records will be reviewed for evidence (eg a letter from hepatology services) that the patient has been enrolled in HCC surveillance. The primary care record review will take place up to 30 months from randomisation to ensure enough time for definitive decisions regarding HCC surveillance to have been made by the clinical team.

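### The base-case model grants the surveillance benefit on referral, with no allowance for whether surveillance takes place

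*Protocol article*

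**What the plan says.** All places are in the Protocol article.

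- **Entry rule** (Cost-effectiveness analysis, base case, text below Figure 2): "In both cohorts, patients identified with liver cirrhosis and referred for HCC surveillance will enter a separate health state", named F4_SURV.
- **Benefit attached to the state** (same paragraph): "participants in this health state who develop HCC will have a higher chance of cure", together with a lower chance of progressing to death or transplantation. The size is not given; it comes from published data, reference 16.
- **Second benefit in the same state**: "a proportion of those in F4_SURV will have a lower risk of progressing to a decompensated state", where the proportion is to reflect how many participants really start beta-blockers.
- **What the source is said to show** (Introduction, also citing reference 16): "cancers that are identified in patients who are undergoing regular surveillance have better outcomes".
- **Trial data fed to the model** (Cost-effectiveness analysis): micro-costs of testing and follow-up, drop-out from the two diagnostic pathways, and "the relative proportions of different stages of liver disease and the demographic characteristics of the cohorts".
- **What the records are checked for** (Primary outcome data collection): "records will be reviewed for evidence (eg a letter from hepatology services) that the patient has been enrolled in HCC surveillance". The review runs up to 30 months from randomisation.

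The ICER and the modelled number of cancer deaths avoided are both secondary outcomes.

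**The concern.** Surveillance can improve cancer outcome only in people who are scanned. The protocol passes through three steps on the way to that benefit: referral (the primary outcome and the model's entry rule), enrolment (what the record review looks for) and regular surveillance (the condition under which the Introduction says outcomes are better). The model attaches the benefit at the first step. The evidence is described at the third, and no stated quantity links the two.

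The plan also treats two benefits in one health state differently. Beta-blocker uptake is scaled to real use; surveillance uptake is not. The paragraph opens by saying that the base case will stay close to actual practice, so the unscaled benefit does not fit the plan's own aim.

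At stake are the modelled cures, the cancer deaths avoided and, through them, the QALY gain of every testing strategy that sends people to surveillance.

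**Working it through.** **Step 1. The texts side by side.**

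| Element | Condition in the text | Scaled to uptake? |
|---|---|---|
| Better cure and progression chances in F4_SURV | Identified with cirrhosis and referred | No |
| Lower decompensation risk in F4_SURV | Beta-blocker started | Yes |
| Benefit as the Introduction describes it | Regular surveillance | Condition is attendance |
| Drop-out listed for the model | Diagnostic pathways only | Surveillance not listed |
| Record review | Enrolment | Scans done not mentioned |

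The plan gives no figure for attendance or for the size of the surveillance effect, so there is no stated result to reproduce.

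**Step 2. Size, if the source estimate is for attenders.** Let n be the cancers arising in F4_SURV, c0 the chance of cure without surveillance, c1 the chance with regular surveillance, and a the fraction attending.

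- Extra cures as written: n × (c1 − c0).
- Extra cures if non-attenders stay at c0: n × a × (c1 − c0).
- Overstatement: 1/a.

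| Assumed attendance a | 1/a |
|---|---|
| 100% | 1.00 |
| 90% | 1.11 |
| 70% | 1.43 |
| 50% | 2.00 |

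The factor applies to the extra cures credited to surveillance, not to all cures. It carries over to cancer deaths avoided in so far as these arise from the F4_SURV cure and progression effect.

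**Step 3. The same in numbers of cancers.** The Abstract gives an HCC incidence of 1% to 2% a year in people with T2DM and cirrhosis. For 100 such people over 10 years, ignoring other deaths:

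- 100 × (1 − 0.99^10) = 9.6 cancers; 100 × (1 − 0.98^10) = 18.3 cancers.
- As written, all 9.6 to 18.3 receive the better chances.
- At an assumed 70% attendance, 0.7 × 9.56 = 6.7 to 0.7 × 18.29 = 12.8 would.
- At an assumed 50%, 4.8 to 9.1 would.

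**Step 4. Comparison between strategies.** The rule applies to both cohorts. With the same attendance in both, the difference in surveillance-related cures between screening and usual care is overstated by the same 1/a. If screen-detected people attend less than those found through usual care, the difference is overstated by more; if they attend more, by less. The documents do not say which.

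**Step 5. Could the trial supply the attendance figure?** Only in part.

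- Referral can fall as late as 12 months and the review runs up to 30, leaving up to 30 − 12 = 18 months, less the time to a hepatology decision. The last recruits (April 2025, with outcome data complete by June 2026) have about 14 months in all.
- Numbers are small. At the Abstract's upper cirrhosis prevalence of 1 in 20, 320 × 0.05 = 16 people in the screening arm. With 16 people and an assumed attendance of 70%, the standard error is √(0.7 × 0.3/16) = 0.115, so a rough 95% range is 70% ± 22 points.

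The trial figure is worth having, but must be varied widely.

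**The case against.** The strongest objection is that the effect size is not stated. The published estimate may already be an average over people enrolled in surveillance, including those who miss scans. In that case multiplying by attendance would count non-attendance twice, and the base case as written would be right. One sentence in the Introduction cannot settle what the source measured. This stands, and it makes the overstatement conditional.

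It is also fair that an article leaves detail to the full model specification, that Figure 2 is not shown, and that probabilistic, one-way and scenario analyses on the main assumptions are planned. They could take in attendance, although the only scenario named concerns a hypothetical anti-fibrotic drug. The entry rule itself is stated, however, and the contrast with the beta-blocker rule lies in the text.

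A reader might infer more than the document supports:

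- **That false positives are credited with cancer cures.** Referral turns on clinical judgement ("the primary outcome will be whether the clinician felt the disease was severe enough to warrant referral for HCC surveillance"), and the work-up varies: "this may include history, examination, no further tests or repeat VCTE, additional tests for fibrosis and in some cases liver biopsy". But the model begins with a diagnostic decision tree and is to resemble earlier models, which the Introduction describes as using preset sensitivity and specificity and counting gain for patients correctly classified. The list of inputs covers data from the study only, so the absence of accuracy figures there shows nothing. Misclassification may already be handled.
- **That neither disease nor surveillance is checked.** Enrolment is looked for in the records, which is more than bare referral, and entry to F4_SURV needs both identification and referral.
- **That the ICER is biased towards screening.** Non-attenders also use fewer scans. Scan costs, treatment costs and utilities are not given, so the net effect cannot be derived.

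**Conclusion.** The point holds in a limited form. As stated, the base case gives the surveillance benefit to everyone identified with cirrhosis and referred. It makes no allowance for attendance, although the protocol links the same source's benefit to regular surveillance and scales the neighbouring beta-blocker benefit to real uptake. If the source estimate is for attenders, the cures and cancer deaths avoided that are credited to surveillance are overstated 1.1-fold to 2.0-fold for an assumed attendance of 90% to 50%. If it is by enrolment, there is no overstatement from this cause. The attendance range is an assumption, and no size can be put on the ICER. Misclassification of the cirrhosis label is not shown to be mishandled; it merits a sensitivity scenario, not a finding of error. This is an inexpensive improvement and does not touch the primary analysis.

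**What to change.** 1. In the record review already planned (up to 30 months), add a field for whether surveillance scans took place.
2. State whether the published surveillance effect is for attenders or for all enrolled. If for attenders, apply the effect and the scan costs to the attending fraction of F4_SURV. If by enrolment, leave the effect unscaled to avoid double counting.
3. Vary attendance in the one-way and probabilistic analyses, with a wide distribution because the trial will supply few surveillance patients.
4. Add a scenario that varies the positive predictive value of the F4 label, with false positives carrying surveillance cost and no HCC benefit. State how the diagnostic tree already treats them.

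**Cost.** One extraction field, one or two model parameters and a little more record work. The figure for cancer deaths avoided will probably look less favourable.
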